**Methods:**

In this multicentre prospective observational study we aim to enrol 100 patients. Multiparametric MRI will be performed prior to NAC, approximately halfway and after completion of NAC. Liquid biopsies will be obtained immediately prior to every cycle of chemotherapy and after completion of NAC. The primary endpoint is RCB in the surgical resection specimen following NAC. Collected data will primarily be analysed using multivariable techniques such as penalised regression techniques.

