### Study design

This is a prospective multicentre observational study in patients with breast cancer undergoing NAC. The study has been approved by the Medical Ethics Review Committee of the University Medical Center Utrecht (19-396, NL67308.041.19). Standard Protocol Items: Recommendations for Interventional Trials guidelines were followed.^29^ In the LIMA study, the complementary expertise of investigators in the MRI and liquid biopsy field have been combined into a consortium. The study participants will be recruited in four different Dutch hospitals. Potential study participants are screened by their treating physicians. Written informed consent will be obtained from all participants by their physician or research nurse. All participants will undergo NAC followed by surgery according to the Dutch oncology guidelines.^30^ Study duration is from diagnosis of invasive breast cancer until the pathological assessment of the resection specimen after surgery.

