#### Surgical resection specimen

Management of the resection specimens will be carried out according to the routine clinical protocol. RCB takes the dimensions of the primary tumour bed into account, as well as cellularity, percentage of in situ disease, number of positive lymph nodes and diameter of the largest lymph node metastases. These items will be reviewed in the surgical resection specimen by a trained pathologist. Calculation of the RCB will be done according to the guidelines and using the calculator provided by the MD Anderson website.^38^

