### Statistical analysis plan

A formal sample size and power calculation are impossible for this type of study with a large number of candidate predictor features in relation to the number patients, because meaningful (co-)variance data is lacking to feed informative simulation studies. Nevertheless, similar studies of this size have succeeded in generating clinically meaningful predictive signatures.^41^ Furthermore, our primary endpoint (RCB) is continuous, increasing the effective sample size compared with a binary outcome (such as pCR). Finally, inclusion of 100 patients is also what we deem feasible based on the number of patients with breast cancer treated with NAC in our region in a 2-year time period.

The primary analysis population will include all patients who receive at least one cycle of neo-adjuvant treatment and have the primary outcome assessed (ie, residual breast cancer burden). Patterns of missing data will be inspected and if necessary we will use established methods for multiple imputation to account for missing data under the missing at random assumption.

To meet our primary objective we will estimate the over-optimism corrected mean square error and associated 95% CIs for predicting RCB in the primary analysis population using all candidate predictors from the clinical data, biopsy data and imaging data with or without the features from the liquid biopsies. These scenarios are tested at three time points: before, half way through and at the end of NAC treatment. We will use the prediction scenarios with and without liquid biopsies features to examine their additive value to the MRI-clinical-pathology-based model.

To develop the optimal and most parsimonious prediction model for each scenario, we will primarily make use of Least Absolute Shrinkage and Selection Operator penalised linear regression techniques, using bootstrapping to obtain the penalty value that minimises the mean square error in RCB prediction. This will be repeated in each imputation dataset, and the optimal models from each imputation dataset will then be averaged to obtain one final optimal model for each analysed scenario. We will repeat all these modelling steps under an additional bootstrap resampling scheme for an additional internal validation step to optimally correct for over-optimism.

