## Discussion

With the neoadjuvant approach, the tumour is left in situ during chemotherapy. The extent to which the tumour of an individual patients responds to NAC is highly variable. This variability in response means a certain NAC regimen could be overtreatment in one patient, but undertreatment in another. To define the right treatment approach for an individual patients, and to correctly balance the treatment related side effects and oncological safety, accurate prediction of response is essential. Response prediction could be used to personalise treatment for breast cancer treated with NAC in different scenarios. After completion of NAC, but before surgery, reliable tumour response evaluation is essential for facilitating de-escalation of the surgical treatment of both breast and axilla. If this evaluation is accurate enough, a wait-and-see approach may even be imaginable, sparing patients surgery-associated morbidity.

When response to NAC is assessed at earlier time points during treatment, it can provide a different set of opportunities for tailoring the treatment to individual patients’ needs. An inadequate tumour response at interim evaluation may guide the treating physicians to opt for a different (non-cross resistant) chemotherapy regimen, choose a different type of systemic treatment, or adapt (the timing of) surgical intervention. Chemotherapy treatment is associated with comorbidities and reduced quality of life in patients with breast cancer. Excellent response at interim evaluation could also be a reason for adapting (the timing of) surgical intervention or may make chemotherapy de-escalation possible, thereby sparing patients unnecessary side effects.

Especially prediction of tumour response before start of any treatment is challenging, but could have a major impact on determining the treatment strategy. Leaving the tumour in situ during NAC can carry risks in aggressive tumours that will not respond to NAC. If this (lack of) response to NAC could be reliably predicted beforehand, more effective treatment options may be adopted.

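### Patients who start NAC but are never operated on because of progression or cancer death drop out of the pre-NAC and halfway evaluations, although non-responders are one target of those predictions

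*Protocol article*

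**What the plan says.** The section Statistical analysis plan of the protocol article sets two conditions for the primary analysis: "The primary analysis population will include all patients who receive at least one cycle of neo-adjuvant treatment and have the primary outcome assessed". The second can be met only after surgery. The abstract says "The primary endpoint is RCB in the surgical resection specimen following NAC", and the section Surgical resection specimen says of the components of the score that "These items will be reviewed in the surgical resection specimen by a trained pathologist".

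The mean square error (MSE) is estimated for "predicting RCB in the primary analysis population using all candidate predictors from the clinical data, biopsy data and imaging data", with or without liquid-biopsy features. On timing, the plan says "These scenarios are tested at three time points: before, half way through and at the end of NAC treatment". So one population serves all three scenarios. On missing data it adds that "if necessary we will use established methods for multiple imputation to account for missing data under the missing at random assumption".

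The section Study design takes it that every participant goes on to surgery: "Study duration is from diagnosis of invasive breast cancer until the pathological assessment of the resection specimen after surgery". The article has no rule for a patient who does not. The Discussion explains why a prediction before treatment matters: "Leaving the tumour in situ during NAC can carry risks in aggressive tumours that will not respond to NAC". It also gives poor response at interim evaluation as one use of the halfway prediction, alongside de-escalation in patients who respond very well.

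**The concern.** A pre-NAC or halfway prediction is made before anyone knows whether the patient will reach surgery. The population rule nevertheless admits her to the evaluation of that prediction only if she did. Progression to inoperable or distant disease, or death from cancer, can prevent surgery, and each is an extreme form of non-response. Selection into the evaluation then depends on the outcome that the model is meant to foresee.

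At stake is how far the reported performance carries over to the patients who would receive the prediction. The MSE and calibration would describe operated patients, while the early models are meant for everyone starting NAC.

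**Working it through.** **Step 1: does the rule remove these patients?**
- RCB is scored on the resection specimen (abstract; Surgical resection specimen). No resection means no RCB.
- The primary population requires an assessed RCB (Statistical analysis plan). No RCB means the patient is not in the analysis.
- The same population is used before, halfway through and at the end of NAC. She is therefore absent from the two early scenarios as well.

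**Step 2: does anything else in the plan bring her back?**
- Multiple imputation: the population already requires an observed outcome, so imputation reaches only missing predictors. If it were extended to RCB, missing at random would be doubtful where progression is the reason for absence.
- Bootstrap optimism correction: it resamples the same selected patients. It corrects for overfitting and cannot correct for selection.
- Calibration, ROC and decision-curve analyses: they compare predictions with observed RCB, so they carry the same exclusion.

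**Step 3: who stays in?** The rule asks for one cycle, not completed NAC. A patient who progresses, stops early and is then operated on has an RCB and is analysed. Only starters without an assessable specimen are lost.

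**Step 4: how large could the effect on the MSE be?** The plan has no figure to reproduce. It gives no rate of non-surgery, no expected MSE and no SD of RCB, and the target of 100 patients rests on feasibility. All inputs below except the 100 are assumptions.
- k = starters per 100 without surgery because of progression or cancer death: 2, 4 or 6
- r = amount by which the model under-predicts a poor RCB value assigned to them: 1.5 to 2.5 units
- M = MSE in operated patients: 1.0 to 1.4

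MSE over all starters = ((100 − k) × M + k × r²) / 100.
Relative change = k × (r² − M) / (100 × M), which is positive whenever r² exceeds M.

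| k | r | M | MSE, all starters | Change |
|---|---|---|---|---|
| 2 | 1.5 | 1.4 | (137.2 + 4.5)/100 = 1.417 | +1.2% |
| 2 | 2.0 | 1.2 | (117.6 + 8.0)/100 = 1.256 | +4.7% |
| 4 | 2.0 | 1.2 | (115.2 + 16.0)/100 = 1.312 | +9.3% |
| 4 | 2.5 | 1.0 | (96.0 + 25.0)/100 = 1.210 | +21% |
| 6 | 2.5 | 1.0 | (94.0 + 37.5)/100 = 1.315 | +31.5% |

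The last two rows pair the largest residual with the smallest MSE. The middle rows use mid-range residual and MSE.

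**Step 5: a check by simulation.** One million simulated patients had a standardised latent burden and one linear predictor score with R² of 0.2, 0.4 or 0.6. Of these, 2%, 5% or 10% were removed, either at random from the worst fifth or as the very worst cases. The model was fitted in those remaining.
- Reported MSE divided by MSE over all starters: 0.72 to 0.99
- Fitted slope divided by true slope: 0.76 to 0.99
- With 5% removed and R² = 0.4: 0.576 against 0.604 (ratio 0.95) for random loss from the worst fifth, and 0.527 against 0.612 (ratio 0.86) for loss of the very worst

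The direction was the same in every scenario. The size depends on the assumed share and selection. ROC, net benefit and the with-versus-without liquid-biopsy contrast were not simulated.

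**The case against.** The strongest objection is that RCB without a specimen is undefined, not merely unobserved. The stated aim is to predict RCB, and the population matches that endpoint. An MSE over all starters needs a value assigned by convention. This stands, and it is why the linear model should remain in patients with RCB.

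The group may also be small. The study enrols early-stage patients, excludes inflammatory cancer and distant metastases on PET/CT, and plans surgery for all. With about 100 patients and roughly normal residuals, the relative standard error of an MSE is about √(2/100) = 14%, so its 95% interval is about ±28%. Most of the range in the table lies within that. This stands too, although selection shifts the estimate and the interval does not reflect the shift.

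A journal article may leave the reporting of missing outcomes to a fuller plan, and the study is exploratory. That covers counts and reasons. It does not cover the population rule, which the article itself fixes.

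Two stronger readings are tempting. A reader might infer that non-responders as a group are deleted, so that the models see only patients who responded well enough for surgery. The documents do not support this: one cycle suffices for entry, and the Discussion allows the timing of surgery to be adapted after a poor interim response. A reader might also infer that liquid biopsies are denied credit for detecting progression. The plan compares models with and without these features in the same patients, and nothing in the documents or in the calculations above shows how that contrast would move.

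**Conclusion.** The point holds in limited form. The rule makes entry to the pre-NAC and halfway evaluations depend on a later, response-related event, and neither the imputation nor the bootstrap repairs this. The likely direction is that reported MSE and calibration are somewhat too favourable for all NAC starters. The size cannot be derived from the documents: about +1% to +32% in MSE under the assumed inputs, and about +5% to +9% with mid-range residual and MSE and 2 to 4 patients lost. It would be negligible if almost everyone is operated on. For discrimination and for the added value of liquid biopsies, neither direction nor size is established. The point is worth acting on because the remedy is cheap and lets readers see how many patients were affected.

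**What to change.** 1. Keep the primary linear RCB model in patients with RCB, and state that its MSE applies to operated patients.
2. For the pre-NAC and halfway scenarios, include all NAC starters in the ROC and decision-curve analyses against RCB subgroups and in the secondary pCR-type outcomes. Count no surgery due to progression or cancer death as the worst RCB subgroup, or as no pCR.
3. Add one sensitivity analysis of the MSE that gives these patients a poor RCB value, for example the highest observed. Label it as a convention.
4. Report the number of starters without RCB and the reason for each.

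The cost is a few lines of analysis wording, one extra run and recording of the reason for no surgery in the eCRF. Reported accuracy may come out slightly less favourable. Treatment and patient procedures are unaffected.

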### Study population

In order to be eligible to participate in the study, a subject must meet all inclusion criteria and none of the exclusion criteria. We aim to include 100 patients.

Inclusion criteria:

Female patients aged 18 years or older.

Histologically proven invasive breast carcinoma.Planned to receive NAC (and in case of a HER2-positive tumour: addition of trastuzumab and/or pertuzumab).

Exclusion criteria:

Breast cancer oestrogen receptor (ER)-positive and HER2-negative by immunohistochemistry and Bloom and Richardson grade 1.Inflammatory breast cancer.Distant metastases on PET/CT.Prior ipsilateral breast cancer (contralateral breast cancer >5 years ago is allowed).Other active malignant diseases in the past 5 years (excluded squamous cell or basal cell carcinoma of the skin).Pregnancy or lactation.Contra-indications for MRI according to standard hospital guidelines.Contra-indications for gadolinium-based contrast-agent, including known prior allergic reaction to any contrast-agent, and renal failure, defined by a glomerular filtration rate <30 mL/min/1.73m^2^.

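### The plan names an MSE with 95% CI for each model, but no estimate or interval for the with-versus-without liquid biopsy difference that answers the additive-value question

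*Protocol article*

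**What the plan says.** All of this is in the Statistical analysis plan section of the protocol article unless stated otherwise.

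- Primary quantity: "we will estimate the over-optimism corrected mean square error and associated 95% CIs for predicting RCB in the primary analysis population".
- Models: "using all candidate predictors from the clinical data, biopsy data and imaging data with or without the features from the liquid biopsies".
- Time points: "These scenarios are tested at three time points: before, half way through and at the end of NAC treatment".
- Comparison: "We will use the prediction scenarios with and without liquid biopsies features to examine their additive value to the MRI-clinical-pathology-based model".
- Size: "We aim to include 100 patients" (Study population). The number rests partly on feasibility ("inclusion of 100 patients is also what we deem feasible based on the number of patients with breast cancer treated with NAC in our region"), and the section states "A formal sample size and power calculation are impossible for this type of study".

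There is one primary analysis population, namely patients with at least one cycle and an assessed RCB. Multiple imputation is planned where needed, and an outer bootstrap repeats all modelling steps to correct for optimism. Calibration, ROC curves and decision curves follow as secondary measures. Neither the primary nor the secondary part names a contrast between the two models, an interval for such a contrast, or a rule for concluding that liquid biopsies add value.

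**The concern.** The additive-value question is about a difference between two models, whereas the named primary quantity describes one model at a time. Followed as written, the plan yields six corrected MSEs with intervals (two models at three time points) and no interval for any of the three increments.

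The gap costs more than presentation. A patient whose RCB is hard to predict is hard for both models, so the two MSEs rise and fall together across samples. Separate intervals carry that shared variation twice, and in a paired difference most of it cancels. The Introduction motivates the study with an earlier study in which adding ctDNA to an MRI predictor gave a numerical gain that was not significant. Two wide intervals side by side could leave the reader in the same position. The sample size was set without a power calculation and partly by what the region can recruit, so lost precision cannot easily be bought back with patients.

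**Working it through.** The plan has no calculation to reproduce: it gives no power, effect size, MSE or error correlation. From the document: n = 100 (the enrolment target), three time points, the same patients in both models. Assumed: normal errors, base-model MSE set to 1, and liquid biopsy features explaining 5% to 30% of the residual variance.

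**1. One MSE at n = 100.** The interval multipliers are 99/χ²(0.975; 99) = 0.771 and 99/χ²(0.025; 99) = 1.349, that is -23% to +35%. The symmetric approximation is 1.96 × √(2/100) = 0.28, or ±28%.

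**2. The difference, by formula.** Let s1 and s2 be the two MSEs and r the correlation of the two models' errors.

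- As if independent: SE = √[(2s1² + 2s2²)/n]
- Paired: SE = √[(2s1² + 2s2² − 4r²s1s2)/n], with r² = s2/s1 for ideal nested models

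For a 20% gain, s1 = 1, s2 = 0.8 and r² = 0.8:

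- Independent: √[(2 + 1.28)/100] = 0.181, half-width 1.96 × 0.181 = 0.35
- Paired: √[(3.28 − 2.56)/100] = 0.085, half-width 1.96 × 0.085 = 0.17

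| Assumed gain | Half-width, independent | Half-width, paired | SE ratio |
|---|---|---|---|
| 5% | 0.38 | 0.09 | 0.23 |
| 10% | 0.37 | 0.12 | 0.32 |
| 15% | 0.36 | 0.15 | 0.40 |
| 20% | 0.35 | 0.17 | 0.47 |
| 30% | 0.34 | 0.20 | 0.59 |

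For a true 20% gain, a difference interval built as if the models were independent excludes zero with probability about 0.03. The paired interval does so with probability about 0.65. If someone did look for non-overlap of the two separate intervals, the probability would be about 0.0002.

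**3. Allowing for refitting.** The formula treats the models as fixed. A LASSO simulation (n = 100, 30 base and 20 added features, 10-fold cross-validated errors, 40 replicates per setting) gives the spread of the difference with refitting included. The variance saved is 1 − (SD/SE)², and the equivalent number of patients is (SE/SD)².

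| Residual variance explained | Error correlation | SE as if independent | Simple paired SE | Empirical SD of difference | SD/SE | Variance saved | Patients equivalent |
|---|---|---|---|---|---|---|---|
| 0% | 0.97 | 0.142 | 0.032 | 0.044 | 0.31 | 90% | 10.4 |
| 10% | 0.95 | 0.145 | 0.044 | 0.069 | 0.48 | 77% | 4.4 |
| 20% | 0.93 | 0.136 | 0.051 | 0.078 | 0.57 | 67% | 3.0 |
| 35% | 0.88 | 0.127 | 0.066 | 0.089 | 0.70 | 51% | 2.0 |

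The simple paired SE is only 64% to 74% of the empirical SD, so it would give an interval that is too narrow.

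**4. Dependence on the correlation.** With equal MSEs the SE ratio is √(1 − r²), so the share of variance saved is r². It is 25% at r = 0.5, 49% at 0.7, 64% at 0.8 and 81% at 0.9. Half is reached at r = √0.5 ≈ 0.71.

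**The case against.** The strongest reply is that the text leaves the method of comparison open. A reader might infer that additive value will be judged by whether two separate intervals overlap. The article does not say so, and it does not exclude a difference. Only a journal article is at hand, and a fuller analysis plan may define the contrast. This stands, and it limits the point to what the section names and does not name. It does not remove the point. The section already fixes the primary quantity, the penalty selection, the averaging over imputations and the outer bootstrap, and the quantity it fixes is not the incremental one.

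A reader might also infer that the study is bound to report no added value. The documents contain no test or decision rule that would force this. The objective is exploratory, the Discussion speaks of proof of concept, and further performance measures are planned. For the same reason, each model's own MSE answers part of the objective and should stay.

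Nor does the design itself lose information: the same patients and the same bootstrap make the paired contrast available. What would be lost is precision in the reported comparison.

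Finally, the simple paired SE would suggest larger savings. SE ratios of 0.23 to 0.52 in the simulation correspond to about 19 to 4 times the patients (1/0.23² and 1/0.52²). Those figures ignore refitting and should not be used.

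**Conclusion.** The point holds in limited form: the plan names a primary quantity for each model and none for the difference it sets out to examine. Allowing for refitting, pairing removes about 51% to 90% of the variance of the difference, equivalent to about 2 to 10 times the patients. The upper end belongs to the setting with no true gain. Where liquid biopsies explain 10% to 35% of the residual variance, the factor is about 4 down to 2.

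These sizes rest on assumed gains, normal independent features, cross-validation in place of the planned bootstrap, and 40 replicates per setting. They also need a high error correlation. That is likely for models sharing all clinical, biopsy and imaging candidates, but the document gives no value. The half-widths use 100 analysed patients and widen if fewer have RCB assessed.

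Pairing does not make a small gain detectable. At 10% of residual variance explained, the mean simulated difference was 0.013 against an SD of 0.069; at 35% it was 0.177 against 0.089.

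**What to change.** At each of the three time points, add the optimism-corrected MSE difference (or ratio) between the models with and without liquid biopsy features, and name it as the primary estimate of additive value.

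- Take its 95% CI from the outer bootstrap already planned. Use the same bootstrap samples and the same imputations for both models, and refit both, including the choice of penalty, in each sample.
- Do not use a simple patient-level paired SE, because it ignores refitting.
- Continue to report each model's corrected MSE and CI, which describe how well each model predicts.

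The cost is a few sentences in the analysis plan and a little more analysis work. No additional patients, visits or samples are needed. If the fuller analysis plan already defines this contrast, it is enough to state it there as the primary estimate of additive value and to confirm how the interval is formed.

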**Aim:**

To combine multiparametric MRI and liquid biopsies in patients with breast cancer to predict residual cancer burden (RCB) after NAC, in adjunct to standard clinico-pathological information. Predictions will be made before the start of NAC, approximately halfway during treatment and after completion of NAC.

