## Methods

### Study objectives

The primary objective is to explore to what extent the combination of multiparametric MRI and liquid biopsies prior to, during and after completion of NAC, are able to predict RCB after NAC in addition to conventional clinical and pathological information.

Secondary objective is to use the strategy from the primary objective to predict alternative outcome measures: ypT0 ypN0 (ie, absence of invasive cancer and in situ cancer in the breast and axillary nodes), ypT0/is ypN0 (ie, absence of invasive cancer in the breast and axillary nodes, irrespective of ductal carcinoma in situ), ypT0/is (ie, absence of invasive cancer in the breast irrespective of ductal carcinoma in situ or nodal involvement) and residual lesion volume on DCE-MRI following NAC.

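### The primary objective concerns what MRI and liquid biopsies together add to routine clinical-pathological data, but the article describes no model without MRI, so that increment is not estimated

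*Protocol article*

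**What the plan says.** Under Study objectives, the Protocol article poses its primary objective as an exploratory question: "to what extent the combination of multiparametric MRI and liquid biopsies prior to, during and after completion of NAC, are able to predict RCB". The outcome is read from the specimen resected once neoadjuvant chemotherapy (NAC) is complete. The yardstick named in the same sentence is routine data, since the prediction is meant to come "in addition to conventional clinical and pathological information". The Aim in the Abstract gives the same reference: the two techniques are combined "in adjunct to standard clinico-pathological information". In both places MRI and liquid biopsies stand together as the new information, and the reference is clinical and pathological data.

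The section Statistical analysis plan ties the analysis to that objective: "To meet our primary objective we will estimate the over-optimism corrected mean square error and associated 95% CIs for predicting RCB". The patients are those of the primary analysis population, and the exercise is repeated before, halfway through and at the end of treatment. Two predictor sets enter, described as "using all candidate predictors from the clinical data, biopsy data and imaging data with or without the features from the liquid biopsies". The scenarios with and without liquid biopsy features are then used "to examine their additive value to the MRI-clinical-pathology-based model".

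The next paragraph adds calibration, receiver operating curves and decision curves for these models, and says that the secondary objectives are handled in a similar way. No scenario without imaging is described.

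**The concern.** The objective and the contrast offered for it have different reference models. The objective's reference is clinical-pathological data. The contrast's reference is clinical-pathological data plus MRI. A reader of the results would learn what liquid biopsy adds once MRI is in the model, but not what the pair adds to information that is available anyway.

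Two outcomes would be hard to interpret. If MRI carries most of the gain, the contrast would be small although the combination improves clearly on routine data. If neither technique helps, the full model could still have a respectable MSE because routine data predict RCB. The Introduction notes that response varies between subtypes, so some predictive content in routine data is to be expected. The Discussion makes larger follow-up studies depend on this study showing proof of concept for the combination, so the distinction matters for what comes next.

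**Working it through.** The plan has no figure to reproduce. It gives no power, alpha, target MSE or assumed effect, and the 100 patients rest mainly on feasibility. The check therefore sets the objective beside the analysis and compares the two increments.

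**Notation.** C = clinical and diagnostic-biopsy (pathology) data, M = MRI features, L = liquid biopsy features.

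**Side by side.**
- Objective: M and L are new and C is the reference. The matching quantity is MSE(C) − MSE(C+M+L).
- Analysis: the models are C+M and C+M+L. The contrast is MSE(C+M) − MSE(C+M+L).
- Number of models: 2 predictor sets × 3 time points = 6. None of them is C alone.

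**Identity.**

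MSE(C) − MSE(C+M+L) = [MSE(C) − MSE(C+M)] + [MSE(C+M) − MSE(C+M+L)]

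The left side is the increment in the objective. The plan estimates the second bracket. The first bracket needs MSE(C), which no described model supplies. The identity holds for any fitting method, LASSO included.

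**Illustration on assumed inputs.** The documents give no variance shares. Assume RCB has variance 1, the three blocks are independent, C explains 20%, L explains 5%, and M explains 0%, 15% or 30%. Population MSE is 1 minus the sum of the shares in the model.

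| M share | MSE(C) | MSE(C+M) | MSE(C+M+L) | Planned contrast | Increment in objective |
|---|---|---|---|---|---|
| 0% | 0.80 | 0.80 | 0.75 | 0.80 − 0.75 = 0.05 | 0.80 − 0.75 = 0.05 |
| 15% | 0.80 | 0.65 | 0.60 | 0.65 − 0.60 = 0.05 | 0.80 − 0.60 = 0.20 |
| 30% | 0.80 | 0.50 | 0.45 | 0.50 − 0.45 = 0.05 | 0.80 − 0.45 = 0.35 |

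The planned contrast is the same in all three rows, while the increment in the objective varies sevenfold (0.35 / 0.05 = 7).

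**The same shares at n = 100.** This was simulated with 5 features per block, ordinary least squares, 500 replicates, and MSE measured on 2,000 new patients per replicate. Differences were taken before rounding.

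| M share | MSE(C) | MSE(C+M) | MSE(C+M+L) | Planned contrast | Increment in objective |
|---|---|---|---|---|---|
| 0% | 0.848 | 0.896 | 0.889 | 0.007 | −0.040 |
| 15% | 0.853 | 0.733 | 0.714 | 0.019 | 0.139 |
| 30% | 0.854 | 0.564 | 0.538 | 0.026 | 0.315 |

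In the first row the contrast is slightly positive although the full model predicts worse than C alone, because uninformative imaging features add noise to both models being compared. So in a finite sample the planned contrast fixes neither the size nor the sign of the increment in the objective. This run used unpenalised regression. LASSO would change the numbers but not the identity.

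**The case against.** The strongest reply is that the objective has a reading that the plan does answer. If MRI and liquid biopsies are simply to be used alongside routine data, the target is the performance of the full model, and its optimism-corrected MSE with a 95% CI delivers that at each time point. This stands as a possible reading, though a less natural one, and even then the absolute MSE does not show what the two techniques contributed.

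A second reply is that the planned contrast fits the rationale. The Introduction lists dynamic contrast-enhanced MRI among methods in daily use, says liquid biopsy is not yet standard during NAC, and names the added value of circulating tumour DNA over MRI as unsettled. This also stands, and it is why the existing contrast should stay. It does not put MRI into the reference that the objective and the Aim name, and the article presents multiparametric MRI as a way to improve accuracy, not as routine information.

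Third, the study is exploratory, with no hypothesis test or decision rule. The article is condensed, and an extra comparator could sit in a document not shown. That limits the consequences. But the article itself says which analysis serves the primary objective, and that analysis does not match it.

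A reader might go further and infer that the primary question is wholly unanswered, or that routine data such as subtype account for all of the model's performance. The documents support neither. The planned contrast and the full model's MSE answer part of the question, and the Introduction says that response varies by subtype, not that subtype alone determines it.

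**Conclusion.** The mismatch is real but partial. As described, the analysis estimates the increment of liquid biopsy over an MRI-clinical-pathology model and the absolute performance of the full model. It does not estimate the increment of MRI plus liquid biopsies over clinical-pathological data, which is the most natural reading of the objective. This follows from the wording and the identity, and needs no numerical assumption.

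The size of the missing part is unknown. In population terms it is zero if MRI adds nothing and may be most of the joint gain if MRI is strong. The figures above only show that the two increments can differ. They rest on assumed variance shares, independent blocks and unpenalised regression, and they do not predict what this study will find. Nor do the documents give grounds for demoting the liquid biopsy contrast, which answers a question that the Introduction raises.

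**What to change.** At each time point, add a scenario with clinical and pathological predictors only, run through the same imputation, LASSO and bootstrap steps. This makes 3 predictor sets × 3 time points = 9 models instead of 6. If the reference uses baseline data only, it is the same model throughout and can be fitted once, giving 7. Report the difference in optimism-corrected MSE between the full model and this reference, with a 95% CI, as the estimate for the stated primary objective. Both models should be refitted on the same bootstrap resamples, so that the interval reflects the pairing. Keep the contrast with and without liquid biopsy features beside it.

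Alternatively, reword the primary objective and the Aim to the added value of liquid biopsies over MRI plus clinical-pathological data. The existing contrast then matches.

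A scenario with liquid biopsy but without MRI is optional and is not needed to cure the mismatch. The cost is extra model runs on data already being collected and one further reported contrast, or a change of wording. The documents give no reason to change the number of patients.
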